## Abstract

**Background:**

Acute myocardial infarction remains a major contributor to global morbidity and mortality. Cardiac rehabilitation is widely recognized as an essential component of the comprehensive medical management for patients with ST-elevation myocardial infarction, especially among those who have undergone percutaneous coronary intervention. Adherence to cardiac rehabilitation encompasses patient collaboration with a healthcare provider, active involvement in the treatment regimen, and persistence in practice, characterized by self-efficacy and relapse prevention. Outpatient cardiac rehabilitation constitutes the second phase of the continuum of care, bridging the inpatient and long-term maintenance stages. However, adherence to outpatient cardiac rehabilitation programs in China remains suboptimal. The factors influencing outpatient cardiac rehabilitation in patients with ST-elevation myocardial infarction after percutaneous coronary intervention have not yet been fully elucidated.

**Aims:**

To investigate the status and influencing factors of adherence to outpatient cardiac rehabilitation in patients with ST-elevation myocardial infarction after percutaneous coronary intervention one month after discharge in China and gain a deeper understanding of this phenomenon of interest.

**Methods:**

An explanatory sequential mixed-methods design will be employed to conduct this study with three phases. The first phase is a quantitative study with a cross-sectional design to assess the level of adherence to outpatient cardiac rehabilitation and related influences based on the Health Belief Model among 198 patients with ST-elevation myocardial infarction after percutaneous coronary intervention in two tertiary hospitals in Zhenjiang, Jiangsu Province, China. The second phase is followed by a qualitative study to explore the patients’ perceived facilitators and barriers to adherence to outpatient cardiac rehabilitation. Purposive sampling, semi-structured interviews, and conventional content analysis approaches will be used to collect and analyze the data. The final phase links to integrating the data and developing a targeted strategy to improve adherence to outpatient cardiac rehabilitation among patients with ST-elevation myocardial infarction after percutaneous coronary intervention. The nominal group technique and "weaving techniques" will be implemented in accordance with the results of the preceding two phases.

**Discussion:**

A targeted strategy to improve outpatient cardiac rehabilitation adherence would be designed considering the factors affecting adherence to outpatient cardiac rehabilitation in patients with ST-elevation myocardial infarction after percutaneous coronary intervention.

**Clinical Trial Registration:**

This study has been registered in the Chinese Clinical Trial Registry: ChiCTR2400080035.

## Background

1

Acute myocardial infarction (AMI) is a leading cause of global morbidity and mortality. In recent years, the incidence and mortality of AMI have steadily increased annually in most countries (1, 2). Traditionally, AMI has been classified into ST-elevation MI (STEMI) and non-ST-elevation MI (NSTEMI) (3). Survivors of AMI in Asian countries have relatively high mortality rates. In China, the mortality rates for hospitalization, 30-day, and 90-day were 4.0%, 5.9%, and 7.6%, respectively (4). AMI also entails a significant financial and social burden, such as missed work, prescription expenses, and hospital stay (5). Percutaneous coronary intervention (PCI) is the preferred treatment for AMI revascularization (6). An increase of 1% in PCI cases was associated with a 0.72% decrease in mortality rate (7). According to data from the Chinese National Center for Cardiovascular Quality Improvement, 86.8% of STEMI patients in tertiary hospitals had reperfusion, with emergency PCI accounting for 98.37% of cases (8). Nonetheless, the hospital mortality rate of patients with STEMI after PCI (STEMI-PCI) reached 5.3% in Shanghai (9, 10) and 26.08% in Hebei (11), and the 30-day mortality rate in Sichuan was 12.7% (12).

The American Heart Association (AHA) underscored the significance of cardiac rehabilitation (CR) in patients with AMI and demanded prompt attention to this worldwide issue (13). CR can be divided into three phases: inpatient, outpatient, and maintenance phase (13). In hospitalized and outpatient patients with recent myocardial infarction (MI), PCI, CABG, stable angina, and similar conditions, the AHA placed a strong emphasis on CR (14). The World Health Organization (WHO) defined “adherence” as “the extent to which a person's behavior – taking medication, following a diet, and/or executing lifestyle changes, corresponds with agreed recommendations from a health care provider” in 2003 (15). After that, scholars proposed a conceptual analysis and delineated “adherence to CR” as “patients' collaboration with a healthcare provider, active involvement in the treatment regimen, and persistence in practice characterized by self-efficacy and relapse-prevention” (16).

Numerous benefits have been empirically supported and thoroughly demonstrated (13, 17, 18). These benefits include cardiac risk prevention (19), reduction of cardiac and all-cause mortality rates by approximately 30% and 15% at 1-year follow-up (14), and improvement of quality of life (QoL) and negative emotions (14, 20). However, hospital-based CR participation rates among eligible outpatient patients globally remain at a low level of 10%–30%, due to obstacles such as low socio-economic position, accessibility, conflicting commitments, and cost (21). As a result, home-based CR has gained popularity in the UK, Canada, and Australia, and the adherence rate of STEMI-PCI patients to OCR has remained between 22% and 80% (22, 23). However, this situation is not optimistic in China. The adherence rate has only reached 7.05%–29.9% (24, 25), although the rate among inpatients was 72.74% (26). Chinese scholars have released a summary of multiple pieces of evidence related to CR (27, 28) and have suggested that patients in stable conditions can more flexibly switch to home-based CR from hospital- or center-based CR to improve adherence with appropriate self-monitoring methods.

Despite the general recognition of the benefits of CR adherence, dropout rates exceed 80% (29, 30). Numerous studies have shown a significant increase in the risk of death and MI when CR programs are not adhered to (13), and the influencing factors are multifactorial and individualistic (31). According to an Australian study, the factors included male sex, employment status, health support, shorter hospital stays, and previous AMI or PCI (23). However, in China, adherence was adversely correlated with age, male sex, hyperlipidemia, and D2B time, but positively connected to educational level and arrhythmia during PCI (25). Additional research has noted that adherence to OCR is statistically influenced by patient recognition (32), depression (33, 34), and self-efficacy (35, 36). Diabetes, smoking, and CR costs (22, 37) were all linked to poor OCR adherence. A qualitative study found that STEMI-PCI patients may not be able to recognize and manage ischemic symptoms immediately, may have psychological problems during the acute and recovery stages (38), as well as often overestimate their level of physical activity after discharged (39). More importantly, few studies have investigated effective strategies for improving the level of adherence to OCR in STEMI-PCI patients. The identification of both facilitators and obstacles to adherence to OCR and the mechanisms involved have not been evaluated.

The Health Belief Model (HBM) (40) is a theoretical framework designed to measure the motivations behind starting and continuing health behaviors. It considers demographic variables, psychological characteristics, patients' beliefs about their health, barriers and beneﬁts for certain health behaviors, self-efficacy, and actions triggered by cues (41). HBM has been widely applied in behavioral prevention (42). Even so, no study has found how STEMI-PCI patients' health beliefs actively initiate health behaviors, how their views matter, or how they adhere to OCR. In addition, there are notable differences in the efficacy of influencing factors in different contexts (e.g., gender and social support) (43). Considering the significance and variances in culture, the economy, and society, an inclusive approach is required to address this issue. A mixed-methods design enables researchers to use a qualitative lens to explain the findings of quantitative results by exploring informants' perceptions in greater detail and, thus, a deeper understanding of the phenomenon than either method alone (44). Therefore, it is important and urgent to determine the level of adherence to OCR in STEMI-PCI patients and related influencing factors based on HBM. This will also serve as a basis for early identification and precise control to improve adherence to OCR, particularly in China.

### Study aim

1.1

This study aims to identify the level and factors influencing adherence to home-based OCR in STEMI-PCI patients within one month after discharge and related influencing factors (quantitative phase), then explore the perceived facilitators and barriers of adherence to OCR (qualitative phase), and finally, gain a deeper understanding to develop target strategies to improve adherence to CR in China.

### Specific objectives

1.2

1.Determining the level and factors influencing adherence to OCR among STEMI-PCI patients one month after discharge in two tertiary hospitals in Zhenjiang, Jiangsu Province, China.2.Exploring perceived facilitators and obstacles of adherence to OCR among STEMI-PCI patients one month after discharge from two tertiary hospitals in Zhenjiang, Jiangsu Province, China.3.Generating a deeper understanding of adherence to OCR in STEMI-PCI patients and developing targeted strategies to improve adherence to OCR.

### Definition of terms for this study

1.3

Adherence to CR is the behavior of AMI-PCI patients who are actively involved in the home-based CR program after discharge. It will be measured using the Chinese version of the Adherence to Cardiac Rehabilitation Scale (C-ACRS), developed by Wen Xiaohui (45), which includes five dimensions: physician-prescribed exercise, medication management, nutrition management, cardiac risk factor modification, and psychological management.

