##### The demographic data sheet (DDS)

2.2.4.1

The researcher will develop a DDS, which will include two parts: demographic data, such as age, sex, marital status, educational level, employment status, and smoking status, and history of illness, such as diabetes, dyslipidemia, length of stay, D2B time, and arrhythmia during PCI. The DDS will be a form of open-ended and closed-ended questions.

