##### The center for epidemiological studies depression scale (CES-D-S)

2.2.4.2

Feng et al. (47) developed a Chinese version of the CES-D-S to measure depression. This scale contains four dimensions with 10 items: physical factors, interpersonal relationships, negative emotions, and positive emotions. The I-CVIs ranged from 0.830–1.000, while the S-CVI was 0.86. CFA showed that the structural validity model achieved adaption (RMSEA <0.08, GFI and CFI >0.90, and CMIN/df <3) (47). Each item is rated on a 4 Likert scale from 0 to 3, with a total score range of 0–30 points. The higher the score, the more severe the depression.

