##### The scale of adherence to cardiac rehabilitation (ACRS)

2.2.4.6

The ACRS was developed by Wen, X.H. (52) based on quality interviews and literature reviews to assess adherence to CR in CHD patients. The ACRS contains 33 items with five subscales: exercise, medication, risk factors, nutritional, and psychological management. The I-CVIs of the scale ranged from 0.80–1.00, while the S-CVI was 0.96. The cumulative variance contribution rate was 60.698%, and the CFA showed good structural validity: *X*^2^ < 0.001, RMSEA = 0.055, CFI = 0.851 (52). The scale responds “yes” or “no” for each item (yes = 1 point, no = 0 points). The total score range of the scale is 0–33 points. The total score is classified into high and low: 33–25 points indicates high adherence to cardiac rehabilitation and 24–0 indicates low adherence to cardiac rehabilitation (45).

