#### Data analysis

2.2.6

IBM SPSS 22.0 software will be used for data analysis. Statistical significance will be set at *p* < 0.05. The data analysis process was as follows:

The independent variables, including demographic variables, psychological characteristics, and the six constructs of the HBM, are described using frequency, percentage, mean, and standard deviation.

Dummy coding will be performed for categorical data. The assumption of logistic regression, including linearity, homoscedasticity, and residual normality, will be checked before entering the data into SPSS. Linearity: The partial regression plot between dependent and independent variables should be random. Homoscedasticity: Check the residual plot of the dependent variable; the scatter plot should be random without a curve pattern. Normality of residuals: Check the histogram of the dependent variable and a standard probability plot. Univariate analysis and binary logistic multivariate statistical analysis will be used to calculate the regression coefficient, odds ratio (OR), and 95% confidence interval of each variable using the stepwise entry method, and the independent risk factors related to adherence to home-based phase 2 CR will be analyzed.

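### Smoking status and depression are candidate predictors of an adherence score that itself counts risk-factor and psychological management, so part of their association with high adherence may be built in

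*Protocol article*

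**What the plan says.** **Outcome.** Section 1.3 defines adherence as patient behaviour in home-based rehabilitation, measured on five dimensions that include "cardiac risk factor modification, and psychological management". Section 2.2.4.6 describes the instrument in the same way: "The ACRS contains 33 items with five subscales: exercise, medication, risk factors, nutritional, and psychological management". Each item scores 1 for yes and 0 for no. The total runs from 0 to 33, with 25–33 classed as high and 0–24 as low adherence. The article gives neither the item wording nor the number of items per subscale.

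**Predictors.** Section 2.2.4.1 collects "demographic data, such as age, sex, marital status, educational level, employment status, and smoking status". It does not say whether smoking means current smoking or smoking before the infarction. Section 2.2.4.2 uses a scale whose authors "developed a Chinese version of the CES-D-S to measure depression". It has 10 items and a total of 0–30, and "The higher the score, the more severe the depression".

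**Model and reading.** Section 2.2.6 names "The independent variables, including demographic variables, psychological characteristics, and the six constructs of the HBM". These enter univariate analysis and then stepwise binary logistic regression at the 0.05 level. The variables found this way are to be read as independent risk factors for adherence to home-based phase 2 rehabilitation.

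**The concern.** The same two domains stand on both sides of the model. If the risk-factor subscale asks whether the patient has stopped smoking, a current smoker loses those points by definition, whatever he or she does about exercise, medication or diet. If the psychological subscale asks about mood, a patient with a high CES-D-S score tends to lose points there in the same way.

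Three features of the design leave this uncorrected:

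- Covariate adjustment does not separate a predictor from items of the outcome that record the same thing. Selection by p-value tends to keep such a predictor.
- Predictors and outcome are self-reported in one sitting of 45–60 minutes in a cross-sectional study (sections 2.2 and 2.2.5), so no time ordering helps.
- The Background already cites smoking and depression as linked to poor adherence. An artefact would look like confirmation.

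At stake is the reading of the main quantitative result. It could be reported that smokers adhere less to rehabilitation when the data show only that smokers fail items about smoking. The interview guide (section 2.3.2) and the phase-three strategies (section 2.4) both draw on these findings.

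**Working it through.** The article has no figure for the overlap, so there is none to reproduce. The check asks how large a built-in association could be, and every setting not attributed to the article is an assumption.

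**Inputs from the article**
- 33 binary items, high adherence at 25 or more (section 2.2.4.6).
- Adherence rates of 7.05% and 29.9% cited for China (Background), used only as calibration points. The article does not say that they are proportions above the ACRS cut-off.
- n = 165, which is 5 × 33, the base sample size. The stated 198 is 165 × 1.20 (section 2.2.1).

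**Assumptions**
- 40% of patients smoke.
- Smoking is unrelated to every item except k items, on which every smoker answers no and every non-smoker yes. This is complete overlap, the extreme case for a given k.

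**Mechanism.** With k such items, a smoker must score 25 on the other 33 − k items, while a non-smoker needs only 25 − k. For k = 2 that is 25 of 31 against 23 of 31. Smoking has changed the threshold and nothing else.

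**Formula.** OR = [a/(1 − a)] / [b/(1 − b)], where a and b are the proportions with high adherence among smokers and non-smokers.

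**Worked case.** The other items are endorsed at 60% with latent item correlation 0.3:
- k = 1: a = 0.275, b = 0.323; OR = 0.379/0.477 = 0.79
- k = 2: a = 0.240, b = 0.337; OR = 0.316/0.508 = 0.62
- k = 3: a = 0.201, b = 0.352; OR = 0.252/0.543 = 0.46

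**Results by setting**

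| Items recording smoking | OR, one-factor logistic model, about 30% adherence | OR, same model, about 7% adherence | OR, probit model, endorsement 60–70%, correlation 0.1–0.3 | Chance of p < 0.05 at n = 165 (probit model) |
|---|---|---|---|---|
| 0 | about 1.0 | about 1.0 | about 1.0 | no built-in effect |
| 1 | 0.76 | 0.73 | 0.65–0.80 | 9–21% |
| 2 | 0.57 | 0.51 | 0.41–0.62 | 26–66% |
| 3 | 0.40 | 0.34 | 0.24–0.48 | 55–96% |

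The logistic model has item intercepts with SD 0.8 and loading 1, calibrated to the two adherence rates. Repeating it with another random draw moved the odds ratios by no more than about 0.02. The last column is for a simple two-group comparison, not for the stepwise model.

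**Depression.** In the logistic model, let 4 or 6 items depend on an independent depression score with slope 1.0 or 1.5, and let nothing else depend on it. The OR per SD of depression is then 0.69–0.85 at about 30% adherence and 0.65–0.82 at about 7%. This applies only if psychological-management items reflect mood.

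**The case against.** The strongest reply is that a shared domain name is not a shared item. The article prints no ACRS item, and with no overlapping item the built-in association is absent. Section 1.3 defines adherence as behaviour, whereas the CES-D-S measures symptoms. A depressed patient who seeks help could answer yes to management items, and a patient without depression could answer no. Smoking status may mean smoking before the infarction, in which case someone who has since quit would do well on risk-factor modification. All of this stands. It makes the point conditional, and it makes the depression half the weaker one.

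The odds ratios assume complete agreement between item and predictor. With a single overlapping item the chance of a significant result is only 9–21%. That also stands.

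A reader might infer that part of any association is necessarily built in, that the phase-three strategies would rest on a tautology, or that smoking and depression should be discarded unless they survive removal of the subscale. The documents support none of these. The overlap is possible but not shown. Phase three also draws on interviews with 20–30 patients and an expert panel with feedback from participants and families. Adherence is deliberately multidimensional, so a factor acting through one component still acts on the construct as defined.

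It may also be said that subscale analyses belong in a fuller document. That does not dispose of the point, because this article itself fixes the outcome, the predictors, the model and the reading of the result, and their combination creates the risk.

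**Conclusion.** The point holds as a risk, not as a demonstrated bias. The article makes both variables candidate predictors of a dichotomised total that counts the two related domains, and it plans to read what the regression retains as independent factors.

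For smoking, the built-in odds ratio would be about 0.7–0.8, 0.5–0.6 or 0.3–0.4 if 1, 2 or 3 of the 33 items simply record it, and about 1.0 if none do. Varying item endorsement and correlation widens these ranges to 0.65–0.80, 0.41–0.62 and 0.24–0.48. The figures rest on 40% smokers, complete overlap on the affected items, no other effect of smoking, and smoking status meaning current smoking. For depression the same logic applies only if the psychological items ask about mood rather than coping. One overlapping smoking item is a modest problem. Two or three could produce a declared factor by themselves.

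**What to change.** In section 2.2.6, keep the primary model and add the following:

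1. Check the ACRS items against the smoking question and the CES-D-S, and state which items overlap, if any. State in section 2.2.4.1 whether smoking status is current or pre-infarction.
2. Analyse smoking against the ACRS sum score without the risk-factor subscale, or without its smoking items. Analyse depression against the sum score without the psychological-management subscale.
3. Report the association of both variables with each subscale.
4. If an association disappears once the overlapping items are removed, report it as confined to that component and not as an independent factor for rehabilitation adherence in general.

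The cost is two extra models on data already collected. The shortened score has no published cut-off, so it has to be analysed as a sum, and its results will not be on the same scale as the primary odds ratios. If the check finds no overlapping item, one sentence saying so settles the matter.

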## Methods/design

2

### Study design

2.1

This study uses a sequential explanatory mixed-method approach for data collection, analysis, and integration of the quantitative and qualitative phases (Figure 1). Based on post-positivism, the mixed-method paradigm combines quantitative and qualitative methods to improve our understanding of OCR adherence in patients undergoing STEMI-PCI. Qualitative data will be expanded to quantitative data in the first phase, and both quantitative and qualitative data will be integrated subsequently. These findings will contribute to targeted strategies for improving adherence to OCR.

**Figure 1 F1:**
[figure not shown]
Study diagram of the sequential explanatory mixed-method approach.

### Phase one: quantitative study

2.2

Phase one is designed as a cross-sectional study that will be carried out to assess the level of adherence to OCR of STEMI-PCI patients one month after discharge from two tertiary hospitals in Zhenjiang, Jiangsu Province, China. Then, the impact of demographic variables, psychological characteristics, health beliefs, and adherence to OCR, as well as the related factors influencing adherence, will be investigated.

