#### Sample size and sampling method

2.2.1

According to the suggestion of Nunnally and Bernstien, selecting 5–10 participants per item is appropriate for multivariate analysis (46) 165 participants will be recruited to unitize the factor analysis for the 33 items of the Scale of Adherence to Cardiac Rehabilitation scale (ACRS). Considering a follow-up attrition rate of 20%, this number will increase to 198.

Following the approval of the research project by the Ethics Committee of the two hospitals, the study will be conducted on 198 participants with AMI after PCI one month after discharge who receive home-based OCR. The researchers will visit two hospitals, identify eligible patients using the hospital information system (HIS) following the proportion (70% and 30%) of the target population in two hospitals, explain the study objectives and brief process to them, and obtain informed consent to participate. Patients will complete the Demographic Data Sheet (DDS).

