#### Data collection

2.2.5

This study will collect quantitative data using questionnaires. The following stages will be implemented to complete the data collection process.
(1)After obtaining permission from the directors of each hospital, the researcher will ask one research coordinator from the cardiac clinic of each hospital and a quiet, private room at the cardiac clinic to collect the form and questionnaires.(2)The researcher will prepare 200 packages, each containing a form and five questionnaires, and explain the data collection process to the research coordinators.(3)The researcher will obtain a list of STEMI PCI patients for follow-up at the outpatient department. The researcher will screen eligible patients and assign numerical codes to replace the patients' names. Subsequently, the researcher will provide a coded list to the research coordinators for subject selection.(4)The research coordinator will schedule an appointment in advance for potential patients at the cardiac clinic after they meet the doctor and explain the study's purposes, procedures, duration, and benefits. If the subjects agree to participate, they will be requested to sign a consent form.(5)The research coordinator distributes the research package to all participants. Each participant will spend 45–60 min completing the questionnaires and will then return the questionnaires and consent form separately in two designated boxes within the room. The research coordinator then checks for the completeness of all documents collected from the boxes and returns them to the researcher every week.

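### Psychosocial scores and adherence are recorded in one sitting, so a single stepwise model cannot support 'impact', 'independent risk factors' or early identification

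*Protocol article*

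**What the plan says.** **Design and timing.** Section 2.2 states: "Phase one is designed as a cross-sectional study that will be carried out to assess the level of adherence to OCR". Section 2.2.1 places the assessment: "the study will be conducted on 198 participants with AMI after PCI one month after discharge who receive home-based OCR".

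**Measurement.** Under Data collection (2.2.5), "The researcher will prepare 200 packages, each containing a form and five questionnaires". The five instruments in sections 2.2.4.2 to 2.2.4.6 are depression, perceived social support, health beliefs, cardiac self-efficacy and the adherence scale (ACRS). They are filled in together: "Each participant will spend 45–60 min completing the questionnaires and will then return the questionnaires and consent form separately". No measurement of mood, support, beliefs or self-efficacy at discharge is described.

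**Claims.** Section 2.2 sets out to investigate "the impact of demographic variables, psychological characteristics, health beliefs, and adherence to OCR", together with what influences adherence. Section 2.2.6 plans univariate analysis, then binary logistic regression with stepwise entry, after which "the independent risk factors related to adherence to home-based phase 2 CR will be analyzed". The Background says of determining adherence and its influencing factors: "This will also serve as a basis for early identification and precise control to improve adherence to OCR". The article nowhere discusses the direction of these relations.

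**The concern.** Four of the explanatory measures are states that can change during rehabilitation, and they are recorded at the same moment as the outcome. The article itself supplies reasons to expect a path from adherence to these scores. The Background lists better quality of life and fewer negative emotions among the benefits of rehabilitation, and it cites a definition of adherence that is itself characterised by self-efficacy.

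Other candidates, such as age, D2B time, arrhythmia during PCI and length of stay, are settled by discharge. Section 2.2.6 makes no distinction between the two kinds and lets them compete in one stepwise selection. Two things can follow:

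- a consequence of adherence is selected and labelled a risk factor;
- its presence shrinks the coefficient of a variable that truly came first.

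Early identification needs predictors that are available before adherence is known. Strategies aimed at a factor assume that the factor drives adherence. A single concurrent model supports neither for the psychosocial scores, and a larger sample would not help.

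**Working it through.** **1. The plan's own figure.** Section 2.2.1: 33 items × 5 = 165, and 165 × 1.2 = 198. Both stated numbers reproduce. They rest on participants per item and do not bear on direction; 165 is used below only as the number analysed.

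**2. Time order of the candidate variables.**

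| Variable | Source | Order relative to adherence |
|---|---|---|
| Age, sex, education, diabetes, dyslipidemia, length of stay, D2B time, arrhythmia during PCI | 2.2.4.1 | Settled by discharge |
| Smoking status, employment status | 2.2.4.1; form in the same package (2.2.5) | Unclear: may reflect the month at home |
| Depression, social support, health beliefs, self-efficacy | 2.2.4.2–2.2.4.5 | Concurrent: order not identifiable |

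**3. Can a purely reversed score be selected?** Assumptions, none of them from the protocol unless stated:
- n = 165;
- the scores have no effect on adherence;
- four scores, mutually correlated 0.3 to 0.5, each raised 0.5 SD by adherence;
- forward selection at 0.05 (the protocol gives the level and says stepwise, but not the direction).

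The adherent share is set to 29.9% or 7.05%, the ends of the Chinese range quoted in the Background.

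| Share adherent | At least one reversed score selected | Self-efficacy itself selected |
|---|---|---|
| 29.9% | about 98–99% | about 28–42% |
| 7.05% | about 67–71% | about 18–22% |

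A repeat run with 1,000 studies per setting agreed to within about three percentage points. For scale, four independent scores with no relation to adherence at all would give at least one nominally significant result in about 1 − 0.95⁴ = 19% of studies, and fewer if positively correlated.

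**4. Can a reversed score weaken a true antecedent?** Assume an antecedent *a* with OR 1.5 per SD (log-odds 0.405). Assume a concurrent score *x* = 0.4*a* + 0.5 × (adherent) + error with SD 0.9, so the residual variance is 0.81. By Bayes' rule, the logistic model containing both has coefficients:
- for *x*: 0.5 / 0.81 = 0.617;
- for *a*: 0.405 − (0.5 × 0.4) / 0.81 = 0.405 − 0.247 = 0.158, an OR of e^0.158 = 1.17.

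The true antecedent falls from OR 1.5 to 1.17, while the score with no effect on adherence gets a strong coefficient. These are population values and do not improve with n.

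**The case against.** The best defence has several parts.

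- **The design is declared.** The article calls phase one cross-sectional and claims no temporal order. 'Independent risk factors' is routine regression language, and a condensed article may leave the usual caveat to the results paper. This stands to the extent that a reader might infer that causal findings will certainly be published. The methods say only that things will be investigated and analysed. It does not remove the mismatch between one sitting and the words chosen.
- **The sentence on 'impact' is loosely built.** It lists adherence among the things whose impact is studied. That is fair, but it adds to the need for rewording.
- **Early identification appears only in the Background.** No methods section assigns it to the regression, and the strategies also draw on interviews and a nominal group. This stands. It is still a stated use of determining the influencing factors, and the regression is the only quantitative analysis that does so.
- **Measured after the outcome?** A reader might infer that the scores are taken after the adherence they explain. Section 1.1 refers to adherence within one month, but the abstract and sections 1.2 and 2.2 refer to one month after discharge, and section 2.2.4.6 gives no recall period for the ACRS. The documents support concurrent measurement and no more, which is enough for the point.
- **The size depends on the model.** With self-efficacy as the only predictor, a 0.5 SD reversed shift is significant in about 82% of studies at 29.9% adherent and about 34% at 7.05%. Those figures should not be attached to the planned stepwise model, where correlated scores compete and self-efficacy enters less often.

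**Conclusion.** The point holds as a mismatch between the measurement schedule and the claims attached to one model. For depression, social support, health beliefs and self-efficacy, direction cannot be established. The variables settled by discharge have a clear time order, though confounding remains possible.

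Under the assumptions shown, selection of at least one purely reversed score is near certain at the higher background adherence rate and more likely than not at the lower. The SD shift and the correlations are assumptions. The two rates come from other Chinese studies and are not the share expected to score 25 or more on the ACRS among patients already in home-based rehabilitation.

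The documents do not support a reading that the cross-sectional design is illegitimate or that the regression is invalid as a description of association. The change is worthwhile because it alters what may be concluded, at little cost.

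**What to change.** In section 2.2.6:

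1. Pre-specify a first model with only variables settled by discharge: age, sex, education, prior diagnoses, length of stay, D2B time and arrhythmia during PCI. Admit smoking and employment only if the form records them as status before or at admission. Base any early-identification statement on this model alone.
2. Add depression, social support, the HBM constructs and self-efficacy as a second block. Report them as concurrent correlates, with a sentence saying that direction cannot be established.

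In sections 2.2 and 2.2.6, replace 'impact' and 'independent risk factors' with 'factors associated with adherence'.

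The cost is one extra model on the same data, if needed a clarified time reference for two items on the demographic form, and a more modest claim for the psychosocial factors. No additional patients or visits are needed.
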